Appendix I)

1.0 HYPOTHESES AND STUDY OBJECTIVES

## 1.1 Hypotheses

1.1.1 In treatment-naïve subjects starting a potent ARV regimen consisting of RAL and FTC/TDF, plasma HIV-1 RNA levels will exhibit steeper declines over the first 14 days of treatment compared to the declines previously seen in subjects receiving the efavirenz (EFV)-based three-drug combinations used in the A5160s and A5166s protocols.

1.1.2 Subjects with more rapid first-phase decay (larger d1) will exhibit poorer CD4+ T-cell restoration, as evidenced by: (a) smaller increases from baseline in CD4+ T-cell counts on day 14, and (b) smaller increases from baseline in CD4+ T-cell counts at week 24.

1.1.3 Subjects with more rapid turnover of central memory T-cells at baseline, will exhibit poorer CD4+ T-cell restoration, as evidenced by: (a) smaller increases from baseline in CD4+ T-cell counts on day 14, and (b) smaller increases from baseline in CD4+ T-cell counts at week 24. Speed of turnover of central memory T-cells will be represented by the proportion of CD45RA-/CD27+ cells (CD4+ or CD8+) that: (c) are in cell cycle (Ki-67+) and/or (d) express one or both activation markers CD38, HLA-DR, as measured at baseline.

1.1.4 The rate of absolute change (slope) in proportions of activated central memory (CM) (CD45RA-CD27+) CD4+ and CD8+ T-cells between baseline and inflection point will correlate inversely with the magnitude of CM and total CD4+ T-cell restoration at day 14 and week 24.

1.1.5 Subjects with more rapid first-phase decay will exhibit more rapid turnover (as manifested by proportions of Ki-67+ cells) of CM T-cells at baseline.

1.1.6 Baseline levels of bacterial 16s DNAs that are reflective of the damaged gut mucosal barrier to translocation will correlate with the baseline proportions of activated CM T-cells.

1.1.7 Baseline plasma HIV-1 RNA levels will correlate with baseline proportions of activated CM T-cells.

1.1.8 A mathematical model that takes into account both plasma levels of HIV-1 RNA and plasma levels of bacterial 16s DNAs will correlate better with baseline levels of immune activation and will predict better the magnitude of CD4+ T-cell restoration (inversely) than will either index alone.

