## 1.3 Secondary Objectives

1.3.1 To compare first-phase viral decay rates for RAL and FTC/TDF to first-phase viral decay rates previously estimated for the superior arms of A5160s (parent study A5142) and A5166s (parent study A5095).

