Viral decay modeling from the Merck 004 study in ARV-naïve subjects revealed that, contrary to expectation, there was not a significant difference in terms of first-phase viral decay in the RAL versus EFV arms, possibly in part because of the sparse sampling schedule obtained on days 1, 14, 29, 57, and 85. It was also reported that the RAL and EFV arms did not differ in second-phase decay rates. Instead, the striking difference appeared to be a longer duration of first-phase decay in the RAL arms versus the EFV arm. Mathematical models suggest that the continued virus generation of the second-phase is due to either (1) new infection via long-lived chronic producer’s infected cells or (2) activation of previously dormant latently infected cells. Data were inconsistent with the model that viral production in the second-phase is from long-lived infected cells.(33)

A cross-sectional analysis of integrase resistance data from the BENCHMRK 1 and 2 studies has been presented. The initial data showed that 32 of 41 subjects tested who experienced virologic failure had new mutations in integrase. These mutations tended to be at either N155H or Q148K/R/H, along with other mutations, with the two primary mutations rarely seen together in a single individual. These mutational patterns were said to be similar to those selected for with *in vitro* passage of wild type virus in the presence of RAL and to be associated with phenotypic resistance.(13;14) Additional cross-sectional and longitudinal data have been reported from a phase II dose-ranging study of RAL in treatment experienced subjects, Merck 005. In this study, 35 of the 38 subjects with virologic failure were found to have mutations in integrase, primarily at Q148H/R/K or N155H, both of which being associated with 10-25-fold reductions in susceptibility. They further demonstrated that with the emergence of additional mutations there were increasing levels of drug resistance.(34) However, interpretation of these data is limited by the fact that much of the second phase of decay for most subjects occurred at plasma HIV-1 RNA levels below the limit of detection of quantification method being used (RT-PCR).

Malignancy (Protocols 004, 005, 018, and 019)

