9.6.2 Secondary Objectives

9.6.2.1 To compare first-phase viral decay rates for RAL and FTC/TDF to first-phase viral decay rates estimated for the superior arms of A5160s and A5166s.

Primary analysis: The Wilcoxon signed rank test will be used to compare subject-specific d1 estimates (obtained as above) to the value 0.67, which was the point estimate from d1 obtained on the (EFV-based) superior arm of ACTG viral dynamics substudy A5166s.

Secondary analyses:

1. In an AT analysis (i.e., restricting the data as described in 9.6.1), plasma HIV-1 RNA levels from A5248 will be combined with data from A5166s and A5160s.(10;45;46) The resulting subject-specific EBEs of d1 will be compared using the permutation-based Kruskal-Wallis test. (In a 2001 simulation study, compared to parametric tests, Ding and Wu conclude that permutation-based tests outperform likelihood-based tests [maintain type I error rate, and are robust to deviations from normality and small amounts of missing data].(9) In the majority of published viral-dynamics applications, the nonparametric Wilcoxon test is used for inference to compare d1’s among 2 groups.)
2. This nonparametric comparison of subject-specific EBEs will be repeated, with additional plasma HIV-1 RNA levels from A5248 subjects: plasma HIV-1 RNA levels obtained after discontinuation or modification of FTC/TDF, and/or after no more than 7 cumulative days of prescribed RAL doses are missed.

9.6.2.2 To estimate the second- and third-phase viral decay rates in treatment-naive subjects receiving RAL and FTC/TDF, and to estimate the times at which subjects' decay rates transition from first to second phase and from second to third phase.

Subject-specific second-phase decay rates will be estimated along with first-phase decay rates as described in 9.6.1 above. Similar estimation and inference procedures will be used to estimate third-phase decay rates, based on single copy assay results for plasma HIV-1 RNA samples obtained during weeks 24 to 72.(20;21) The primary analysis will be AT; a secondary analysis may be conducted wherein subjects who discontinued or interrupted the regimen are retained.

Times of transition from first to second phase and from second to third phase will be estimated using the methods of Bosch and colleagues(47) applied to subject-specific predicted log10 HIV-1 RNA from days 0-56 (first to second phase) and applied to log10 HIV-1 RNA.

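### Hypothesis 1.1.1 concerns HIV-1 RNA decline over 14 days, but only d1 is compared with the efavirenz arms, so an advantage that is mainly a longer first phase would not show

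*Protocol*

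**What the plan says.** Protocol 1.1.1 states the hypothesis over a time window: "plasma HIV-1 RNA levels will exhibit steeper declines over the first 14 days of treatment compared to the declines previously seen" in the EFV-based combinations of A5160s and A5166s. Objective 1.3.1 is narrower: "To compare first-phase viral decay rates for RAL and FTC/TDF to first-phase viral decay rates previously estimated for the superior arms" of those substudies.

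Section 9.6.2.1 lists three comparisons, all on subject-specific d1:
- a signed rank test against the fixed value 0.67 ("The Wilcoxon signed rank test will be used to compare subject-specific d1 estimates");
- a permutation-based Kruskal-Wallis test after the RNA data are combined with those of A5166s and A5160s;
- the same nonparametric comparison with additional A5248 RNA values.

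Section 9.6.2.2 estimates the time of transition from first to second phase in A5248 and sets no comparison with the EFV arms. Day-7 RNA change appears under the pharmacokinetic objective (1.3.7, 9.6.2.7).

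On earlier treatment-naive data (Merck 004), section 2.1 says that "contrary to expectation, there was not a significant difference in terms of first-phase viral decay in the RAL versus EFV arms". As a partial explanation it offers the thin sampling in that trial, which had no visit between days 1 and 14. Second-phase rates are likewise described as no different between the two drugs. The contrast that section 2.1 does draw is that "the striking difference appeared to be a longer duration of first-phase decay in the RAL arms versus the EFV arm". A later sentence in the same part cautions that, for most subjects, much of the second phase fell below the detection limit of the assay used.

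**The concern.** The fall in RNA by day 14 depends on how fast the first phase runs and on how long it lasts before the slower second phase takes over. The one feature that the background singles out as separating RAL from EFV is the duration, and no comparison with the EFV arms uses it. If the earlier observation is right, d1 would be about equal, the planned tests would be null, and the trial would hold the RNA data to show a larger 14-day decline without a stated comparison that can see it.

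**Working it through.** **1. The plan's own figure.** Inputs from Protocol 9.4: mean d1 0.80, SD 0.20, n = 30, reference 0.65, 95% CI. The standard error is 0.20/√30 = 0.0365, and the noncentrality is (0.80 − 0.65)/0.0365 = 4.11. The normal approximation gives Φ(4.11 − 1.96) = 98.4%, and the noncentral t gives 98%, as stated. All 30 cells of Table 8 reproduce. The figure presupposes that d1 itself rises to 0.80.

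**2. The planned test against 0.67.** Simulated signed rank test, n = 30, SD 0.20, two-sided 0.05 (assumed, since no level is stated):

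| True mean d1 | Probability of rejection |
| --- | --- |
| 0.80 | 92% |
| 0.75 | 55% |
| 0.70 | 12% |
| 0.67 | about 5% (about 2.5% in favour of RAL) |

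The last row is the case of equal d1 with a longer first phase.

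**3. What equal d1 can hide.** Biexponential curve, where f is the second-phase share of baseline virus:
- V(t)/V0 = (1 − f)·exp(−d1·t) + f·exp(−d2·t)
- crossing day = ln((1 − f)/f)/(d1 − d2)

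d1 = 0.67/day is the protocol's reference. The values of d2 and f are assumptions. The protocol gives neither, and gives no EFV transition time.

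With d2 = 0.04/day:

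| f | Crossing day | Day-14 decline (log10) |
| --- | --- | --- |
| 1% | ln(99)/0.63 = 7.3 | 2.24 |
| 0.5% | ln(199)/0.63 = 8.4 | 2.53 |
| 0.3% | ln(332.3)/0.63 = 9.2 | 2.75 |

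Moving f from 1% to 0.5% adds 2.53 − 2.24 = 0.29 log10. Moving it to 0.3% adds 2.75 − 2.24 = 0.51 log10. The difference in d1 is zero in both. Over d2 = 0.03 to 0.05/day, the decline is 2.18 to 2.30 log10 at f = 1% and 2.69 to 2.80 log10 at f = 0.3%.

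**4. Detectability.** Simulation with n = 30, d2 = 0.04/day, SD of d1 0.10 or 0.20, SD of ln f 0.5, assay SD 0.2 log10, and f falling from 1% to 0.5% or 0.3%, or from 0.5% to 0.25% or 0.15%. The mean day-14 decline is 0.25 to 0.49 log10 larger. A signed rank test on day-14 change rejects in 93% to 100% of runs, and the d1 test in 4% to 5%. The EFV reference was treated as fixed and each d1 as known without error, so the 93% to 100% is optimistic for a comparison with pooled arms.

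**5. Why assay limits matter.** Screening RNA is 10,000 to 300,000 copies/mL. A decline of 2.75 log10 takes any baseline below 50 × 10^2.75 ≈ 28,000 copies/mL under 50 copies/mL by day 14. At 2.24 log10 that threshold is 50 × 10^2.24 ≈ 8,700, below the entry minimum. Values cut off at 50 would therefore shrink a true difference. Section 9.6.1 re-assays such A5248 samples by single copy assay. The protocol does not say whether A5160s or A5166s did so.

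**The case against.** The choice of d1 is reasoned. Section 2.1 gives its theoretical basis and reports that d1 differences tracked long-term outcome in A5166s and A5160s. Objective 1.3.1 and section 9.6.2.1 agree with each other. "plasma HIV-1 RNA levels will exhibit steeper declines over the first 14 days of treatment" can be read as a statement about slope, and section 2.1 links the hypothesis to first-phase rates. The trial is a single-arm pilot whose primary aim is estimation, and a longer first phase would still appear descriptively in the transition times of 9.6.2.2. All of this stands, and it is why d1 should stay.

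A reader might infer that RAL has been shown to prolong the first phase rather than steepen it. The protocol does not support that. It reports no significant difference in rate, names sparse sampling as a possible part of the reason, and notes that much of the second phase was below detection. A5248 samples on days 0, 2, 7, 10, 14 and 21 and may find a d1 difference where the earlier schedule could not.

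A reader might also infer that a null d1 test would lead to rejection of hypothesis 1.1.1. No such rule is written.

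What remains is that the protocol fixes the list of comparisons, hypothesis 1.1.1 names a 14-day window, and nothing on the list responds to first-phase duration. Transition times from A5248 alone cannot answer a question about EFV.

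**Conclusion.** The point holds as a cheap improvement. It is neither a contradiction nor an error in any stated figure, and the primary objective and Tables 7 and 8 are unaffected. If the RAL effect is mainly a longer first phase, the planned comparisons with the EFV arms have no power for it beyond their error rate.

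The size is illustrative only: about 0.25 to 0.5 log10 at day 14, under assumed d2 of 0.03 to 0.05/day and second-phase shares of 0.15% to 1%. It also requires the EFV first phase to end before about day 14, which the assumed values imply and the protocol does not state. The 0.5 log10 end should not be quoted as an expected effect.

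**What to change.** In Protocol 9.6.2.1, from the pooled RNA data already planned:
- Add a pre-specified secondary comparison with the EFV superior arms of log10 HIV-1 RNA change from baseline to day 14, taken from the model at exactly day 14 because the visit window is ±2 days. Use a common lower limit or the same censoring method in all three studies.
- Add an exploratory comparison of the first-to-second phase transition time, or of the second-phase intercept.
- State that the d1 result is read beside these, and that hypothesis 1.1.1 is not judged from d1 alone.

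The cost is wording and two further secondary or exploratory contrasts. No new A5248 samples or subjects are needed. The downside is that assay limits and sampling schedules may not be comparable across the studies. This is most serious for transition time, which is why that contrast should stay exploratory.

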# 3.0 STUDY DESIGN

A5248 is a prospective, open-label, multicenter, 72-week pilot study designed to estimate the first-phase viral decay rate in subjects receiving RAL and FTC/TDF. HIV-infected ARV-naïve subjects (defined as no previous ARV treatment at any time prior to entry) with plasma HIV-1 RNA levels ≥10,000 and ≤ 300,000 copies/mL obtained within 42 days prior to study entry will be enrolled. Subjects will be ineligible if the screening genotype shows the existence of major NRTI, NNRTI, or PI resistance mutations. There will be no CD4+ T-cell count restriction.

Thirty-four subjects will each be followed for 72 weeks. It is anticipated that the 34 subjects will be accrued within 8 months of the study opening to accrual. Subjects will have plasma HIV-1 RNA and CD4+ T-cell count measurements at pre-entry and entry. The geometric and arithmetic means, respectively, of these measurements will be used to establish their baseline values.

Real-time genotyping for drug resistance will be performed at screening, if not already available, and at the time of virologic failure. The study will provide all the resistance assays. Subjects will also undergo frequent routine safety monitoring, including hematology, chemistry evaluations, and urinalyses.

Virologic failure will be defined as a confirmed plasma HIV-1 RNA level ≥ 1000 copies/mL at or after 16 weeks and before 24 weeks, or ≥ 200 copies/mL at or after 24 weeks.

When a subject is suspected to have virologic failure, a confirmatory HIV-1 RNA and a plasma sample for real-time plasma HIV-1 RNA genotype will be collected within 14 days. The specimen collected for genotype at that visit will be sent for resistance testing once virologic failure has been confirmed. It is recommended that subjects continue their regimen while genotypic resistance testing is being performed.

Adherence to all study drugs will be monitored by self-report as per the Schedule of Events. All subjects should be provided adherence reinforcement throughout the study, according to local standard practice. Subjects with poor adherence will be provided counseling by the site. Trough plasma samples will be collected from all subjects for PK analyses (see section 10.0).

Subjects who modify the study regimen or miss doses are expected to stay on study and will be followed; however, in some situations, subjects will be replaced (see section 9.1).

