6.2.2 On-Study Evaluations

Entry (Week 0)

Entry evaluations must occur at least 48 hours after pre-entry evaluations and be completed prior to the initiation of study medications. Subjects must begin treatment on day 0 after study enrollment and after the entry evaluations have been completed.

Post-Entry

After entry, study visits up to day 7 must be scheduled within 1 day of the visit indicated in the schedule of events. Visits scheduled for days 10, 14, and 21 must be scheduled within 2 days, and for days 28 and 56 within 3 days, of the visit indicated in the schedule of events. All visits thereafter must be scheduled within 7 days of the visit indicated in the schedule of events.

Visit to Confirm a Suspected Virologic Failure

Subjects with a plasma HIV-1 RNA level ≥ 1000 copies/mL at or after 16 weeks and before 24 weeks, or ≥ 200 copies/mL at or after 24 weeks, will have a confirmatory plasma HIV-1 RNA test within 14 days after the initial plasma HIV-1 RNA sample indicating suspected virologic failure was obtained. Subjects who have their first detectable plasma HIV-1 RNA level at week 72 will not return for a confirmatory visit and will be considered treatment failures.

Subjects who have a confirmed virologic failure will report to the clinic to have the final visit evaluations performed and will be removed from the study.

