## 8.2 Premature Study Discontinuation

- Subject misses 3 consecutive clinic visits.
- Between weeks 12 and 72, subject misses more than 25% of study medications (since the last visit, self-report).
- Request by the subject to withdraw.
- Request of the primary care provider if s/he thinks the study is no longer in the best interest of the subject.
- Subject judged by the investigator to be at significant risk of failing to comply with the provisions of the protocol as to cause harm to self or seriously interfere with the validity of the study results.
- A defined study endpoint reached (virologic failure as defined in section 3.0)*.*
- At the discretion of the ACTG, IRB, Food and Drug Administration (FDA), Office for Human Research Protections (OHRP), NIAID, investigator, or pharmaceutical supporter.

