9.2.2 Secondary Endpoints

9.2.2.1 Population- and subject-specific first-phase plasma HIV-1 RNA level decay rates d1 (as estimated from biexponential decay models fit to plasma HIV-1 RNA level data through day 56).

9.2.2.2 Population- and subject-specific second-phase viral load decay rates d2 (as estimated from biexponential decay models fit to viral load data through day 56); population- and subject-specific third-phase decay rates d3 as estimated from plasma HIV-1 RNA levels obtained during weeks 24 to 72.

9.2.2.3 Proportion of subjects with viral load <50 copies/mL 24, 48, and 72 weeks after initiation of RAL and FTC/TDF. If the first detectable viral load corresponds to the sample collected at the last visit, the subject will be counted as detectable (at this visit) without confirmation.

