9.6.2.3 To determine the proportion of subjects with plasma HIV-1 RNA below the limit of detection, <50 copies/mL, 24, 48, and 72 weeks after initiation of RAL and FTC/TDF.

The primary analysis will be an ITT analysis, wherein (1) if the study regimen (RAL and/or FTC/TDF) is modified or discontinued, the subject is retained in analyses, and (2) if a subject is lost to follow-up, the last observation is carried forward for subsequent time points. The proportion of subjects with plasma HIV-1 RNA <50 copies/mL at weeks 24, 48, and 72 will be reported along with the exact binomial 95% CI.

A secondary AT analysis will include only those subjects on the study regimen at the time of the evaluation.

9.6.2.4 To evaluate the safety and tolerability of the treatment with RAL and FTC/TDF.

Among subjects taking one or more doses of study drug, the proportion exhibiting each category of events will be reported, along with exact binomial 95% CI. Incidence rates, i.e., numbers of events per person-months of follow-up, will also be reported.

9.6.2.5 To evaluate changes in CD4+ T-cell counts 24, 48, and 72 weeks after initiation of RAL and FTC/TDF.

For the primary analysis, using the ITT approach described in 9.6.2.3, changes in CD4+ T-cell counts at weeks 24, 48, and 72 will be summarized descriptively via mean, SD, median, and quartiles. A secondary AT analysis may also be performed.

9.6.2.6 To investigate the occurrence of RAL and FTC/TDF-resistance mutations at virologic failure using very sensitive resistance assay techniques

Among subjects who took any dose of study drug, for each failing subject, the list of resistance mutations present at failure, if any, will be displayed. Of failing subjects, the proportion with specific mutations (ones occurring frequently among A5248 failures, ones known to be associated with RAL resistance) will be reported along with exact binomial 95% CIs.

9.6.2.7 To evaluate the relationship of RAL and FTC/TDF PK parameters with virologic and immunologic responses, including day 7 plasma HIV-1 RNA change from baseline and the magnitude and slope of changes in CD4+ T-cell counts over the first 14 days of study drug.

RAL, TDF, and FTC PK trough averages at steady state will be estimated.

9.6.2.8 To evaluate adherence by self-report in treatment-naïve subjects receiving RAL and FTC/TDF.

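### The secondary as-treated analysis of HIV-1 RNA <50 copies/mL drops earlier confirmed virologic failures from its denominator, which biases the rate upward, mainly at weeks 48 and 72

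*Protocol*

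**What the plan says.** Section 9.2.2.3 defines the endpoint: "Proportion of subjects with viral load <50 copies/mL 24, 48, and 72 weeks after initiation of RAL and FTC/TDF". Section 9.6.2.3 makes the ITT analysis primary: subjects who modify or discontinue the regimen are retained, and the last observation is carried forward for those lost to follow-up. It then adds: "A secondary AT analysis will include only those subjects on the study regimen at the time of the evaluation".

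Section 3.0 sets the failure rule for the earlier window: "Virologic failure will be defined as a confirmed plasma HIV-1 RNA level ≥ 1000 copies/mL at or after 16 weeks and before 24 weeks". From week 24 onward the confirmed threshold drops to 200 copies/mL. Section 6.2.2 says that subjects with confirmed failure "will report to the clinic to have the final visit evaluations performed and will be removed from the study". Section 8.2 also lists virologic failure among the reasons for premature study discontinuation.

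For a first detectable value at the last visit, section 9.2.2.3 says that "the subject will be counted as detectable (at this visit) without confirmation". No section says how the AT analysis treats a subject removed earlier for confirmed failure.

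**The concern.** Membership of the AT denominator depends on the outcome being measured. A confirmed high HIV-1 RNA ends study participation, and the later AT proportions are then computed among those who remain. The figure answers a narrower question than its label suggests: of subjects on regimen who have not already failed, how many are suppressed?

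The treatment of failures is also uneven. An unconfirmed first detection at week 72 counts against suppression at week 72. A failure confirmed after the week 36 sample, which is stronger evidence, has no place in the week 72 AT proportion.

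At stake is the reading of objective 1.3.3. An AT rate printed beside the ITT rate could be taken as independent support for it, although the AT rate leaves out earlier on-treatment failures. With about 30 subjects, each one left out moves the rate by several points.

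**Working it through.** **Plan's own figure.** There is none to reproduce: the protocol gives no expected suppression or failure rate for this endpoint. The nearest number, in section 2.1, is 85-95% of raltegravir recipients <50 copies/mL at week 24 across four doses in an earlier trial. It is not a confirmed-failure rate and does not reach week 48 or 72, so it cannot fix the inputs below.

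**Who has already left, by visit** (sampling weeks from section 6.1, confirmation within 14 days from section 6.2.2):
- Week 24: only failures confirmed at ≥1000 copies/mL from the week 16 or 20 samples.
- Week 48: those, plus failures first seen at week 24 or 36 (≥200 copies/mL).
- Week 72: those, plus failures first seen at week 48 or 60.

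**Who stays and counts as not suppressed:**
- subjects on regimen at 50-199 copies/mL;
- a rise at the visit that is not, or not yet, confirmed;
- at week 24, subjects at 200-999 copies/mL at weeks 16 and 20 who are still at 50 copies/mL or more;
- a failure first seen at the analysis visit, including a first detection at week 72.

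**Size.** Inputs:
- N = 34 (section 9.4).
- F = failures confirmed on regimen and removed before the visit; assumed 2, 4 or 6.
- L = other subjects on regimen at ≥50 copies/mL at the visit; assumed 0 to 4.
- No other losses (assumed).

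Formulas, with S = N − F − L suppressed:
- AT rate as written = S / (N − F)
- Rate counting failures = S / N
- Excess = S × F / [N × (N − F)]

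| F | L | AT as written | Counting failures | Excess (points) |
|---|---|---|---|---|
| 2 | 0 | 32/32 = 100% | 32/34 = 94.1% | 5.9 |
| 2 | 2 | 30/32 = 93.8% | 30/34 = 88.2% | 5.5 |
| 2 | 4 | 28/32 = 87.5% | 28/34 = 82.4% | 5.1 |
| 4 | 0 | 30/30 = 100% | 30/34 = 88.2% | 11.8 |
| 4 | 2 | 28/30 = 93.3% | 28/34 = 82.4% | 11.0 |
| 4 | 4 | 26/30 = 86.7% | 26/34 = 76.5% | 10.2 |
| 6 | 0 | 28/28 = 100% | 28/34 = 82.4% | 17.6 |
| 6 | 2 | 26/28 = 92.9% | 26/34 = 76.5% | 16.4 |
| 6 | 4 | 24/28 = 85.7% | 24/34 = 70.6% | 15.1 |

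Exact (Clopper-Pearson) 95% intervals for F = 4, L = 2 are 77.9-99.2% as written and 65.5-93.2% counting failures. They overlap, as expected at this sample size, but the shift is systematic and not sampling error.

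The excess is positive whenever F > 0 and S > 0. The AT rate is 100% only when L = 0. With L from 1 to 4 and F from 2 to 6 it runs from 24/28 = 85.7% to 31/32 = 96.9%.

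**Other losses.** Suppose 3 subjects are also off regimen for reasons unrelated to failure, with F = 4 and L = 2. Then 34 − 3 − 4 = 27 are on regimen and 25 are suppressed. The AT rate is 25/27 = 92.6%, against 25/31 = 80.6% counting failures: an excess of 12.0 points, close to the 11.0 without those losses.

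**The case against.** **The analysis is secondary and openly conditional.** This stands in part. The ITT analysis is primary, no test or decision rests on the AT rate, and the study is a single-arm pilot whose primary endpoint is first-phase decay. That limits the weight of the point. It does not remove the selection, since nothing warns the reader that being on regimen at a visit also means not having failed before it.

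**Failures appear elsewhere.** Also true. Section 9.6.2.6 lists mutations for each failing subject, and section 9.2.2.4 reports discontinuation both for any reason and for reasons other than failure. The ITT rate should show failures too, if carry-forward is meant to cover subjects removed for failure. Section 9.6.2.3 mentions it only for loss to follow-up.

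**Subjects may still be taking the drugs.** Section 3.0 recommends continuing while genotyping is done. Section 6.2.2 nevertheless removes confirmed failures, so no later study visit exists at which they could be counted.

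**Counting failures forward changes the quantity estimated.** This is fair. An observed on-regimen proportion is a legitimate summary if it is labelled as conditional on no earlier confirmed failure. It is not so labelled.

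**A stronger reading to avoid.** A reader might infer that the AT rate must come out at or near 100%. The documents do not support that: removal needs a confirmed value of ≥1000 or ≥200 copies/mL, while success needs <50, so several groups on regimen still count against suppression.

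**Conclusion.** The point holds as an upward bias. Two stated rules together, AT restricted to subjects on regimen at the visit and removal of confirmed failures, take earlier on-treatment failures out of the AT denominator. The effect falls mainly on weeks 48 and 72. At week 24 it is confined to confirmed values of ≥1000 copies/mL from two earlier samples.

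The size of about 5 to 18 points is illustrative. It rests on assumed values of F and L and on every F being a failure confirmed on the regimen; the protocol supplies neither rate. If nobody fails before the visit, there is no bias. Because the affected analysis is secondary, the point is minor to moderate.

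**What to change.** Replace the AT sentence in section 9.6.2.3 with wording to this effect: in the AT analysis, subjects whose virologic failure (section 3.0) was confirmed while on the study regimen are counted as not <50 copies/mL at that and all later time points; only subjects who stopped or changed the regimen for other reasons are excluded after stopping.

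If the sponsor prefers the observed on-regimen proportion, the minimum is to label it as conditional on no earlier confirmed failure and to report beside it the number removed for failure before each visit.

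The cost is one sentence. No new data are needed, since regimen changes and HIV-1 RNA are already recorded, and subject management does not change. The downside is a less favourable secondary rate.
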